# Effect of ice-lollies on the recovery time after anaesthesia: protocol for a cluster-randomised trial (Icesthesia)

**DOI:** 10.1186/s13741-026-00668-3

**Published:** 2026-03-19

**Keywords:** Operating room performance, Post-anaesthesia care unit, Postoperative delirium, Postoperative nausea and vomiting, Postoperative pain, Recovery time; supportive care

## Abstract

**Background:**

Effective management in the post-anaesthesia care unit (PACU) is essential to ensure patient safety, comfort, and timely progression through the surgical care pathway. Many patients experience side effects such as nausea, vomiting, sore throat, hoarseness, dizziness, and disorientation. These symptoms can prolong recovery time. Ice-lollies are a pragmatic, non-pharmacologic intervention. We aim to test the hypothesis that offering ice-lollies in the PACU shorten the patients' length of stay in post-anaesthesia care.

**Methods:**

Icesthesia is a prospective monocentric cluster-randomised single-blinded controlled clinical superiority trial in 3140 patients admitted to the PACU of a large university medical centre after anaesthesia. Days are randomised to intervention days with ice-lollies plus standard of care and control days with standard of care only. Anonymised patient data is collected. The primary outcome is the length of time spent in the PACU until decision to discharge. Secondary outcomes are pain medication consumption, nausea and vomiting, and postoperative delirium at discharge.

**Discussion:**

This trial determines if offering ice-lollies to patients postoperatively reduces the length of stay in the PACU compared to standard of care.

**Trial registration:**

German Clinical Trials Register (DRKS00037179) on 11th June 2025.

**Supplementary Information:**

The online version contains supplementary material available at 10.1186/s13741-026-00668-3.

## Background

In the post-anaesthesia care unit (PACU), healthcare staff provide close observation and supportive care until patients regain stable vital signs and are sufficiently alert. Effective management in the PACU is essential to ensure patient safety, comfort, and timely progression through the surgical care pathway. After undergoing anaesthesia, many patients experience side effects such as nausea, vomiting, sore throat, hoarseness, dizziness, and disorientation. These symptoms can delay recovery and prolong the time needed before patients can safely return to their hospital ward or be discharged. Amongst the most common complaints after anaesthesia are sore throat or hoarseness. (Lehmann et al. 2010; Maruyama et al. 2004) Ice-lollies are a non-pharmacologic intervention in the PACU after surgery. They may have a beneficial effect on recovery: the temperature serves as cryotherapy, holding an ice lolly requires attention and keeps patients busy, ice lollies are often associated with positive childhood memories that can take away the focus from boredom, pain and nausea. There is limited evidence that this intervention reduces pain and emergence agitation in children after oral surgery (Sylvester et al. 2011) (Liang et al. 2023) However, if ice-lollies speed up recovery leading to faster discharge to the ward in a general surgical population is unclear. Therefore, we designed a prospective, single blinded monocentric trial investigating the effect of ice-lollies in the PACU on patients' length of stay. The hypothesis is that offering ice-lollies to postoperative patients leads to a faster recovery from the side effects of anaesthesia, thereby reducing the length of stay in the PACU. Secondary outcomes are the effect on consumption of pain medication, nausea and vomiting, and postoperative delirium.

## Methods/design

### Trial design

The proposed trial will be conducted according to the ethical principles based on the Declaration of Helsinki (World Medical Association Declaration of Helsinki 2013) and the guidelines of the International Council for Harmonisation Good Clinical Practice. The trial was approved by the local ethics committee (Ethikkommission bei der Medizinischen Fakultät der LMU München, chairperson [name]) under the registration number #25–0350. The trial was registered in the German Clinical Trials Register (DRKS00037179) on June 11, 2025.

Icesthesia is a single centre cluster-randomised single-blinded (with blinding to the primary outcome) controlled clinical superiority trial in 3,140 patients admitted to the PACU after anaesthesia. The study takes place at the LMU University hospital in Munich, Germany. This protocol is reported in accordance with the SPIRIT (Standard Protocol Items: Recommendations for Interventional Trials) guidelines.

### Patients

We will include patients from the age of 2 treated in the 25-bed PACU after surgery on workdays in one of the following specialties: neurosurgery, orthopaedic surgery, trauma surgery or ear-nose-throat (ENT) surgery. Patients are excluded from the study if they are not permitted oral intake of fluids or food including those with swallowing difficulties or other contraindications to safe oral consumption, or if they are transferred to an intermediate or intensive care unit postoperatively. Both elective and emergent procedures are included.

### Protocol

As this is a cluster randomized design with anonymised data collection with a minimal-risk, non-pharmacologic intervention, the requirement for individual informed consent was waived by the ethics committee. The intervention consists of offering ice lollies (water-based frozen confectionery with sugar and orange flavour) in addition to routinely provided refreshments in the PACU. The ice lollies are a commercially available product (Capri®, Langnese) supplied through the hospital food service in compliance with frozen food storage requirements. All ice lollies are identical in flavour and composition. One ice lolly (55 ml) contains 54 kcal and 12 g of carbohydrates, all of which are sugars. This represents a minor modification of standard care and does not involve any medical procedures or relevant nutritional changes. Given the cluster-level implementation within routine clinical workflow, obtaining individual consent was considered impracticable.

Every morning, the study day is randomised via a web-based randomisation tool (studyrandomizer.com, Rotterdam, Netherlands).(Study Randomizer 2017) Study days are randomized in a 1:1 ratio using permuted blocks with variable block sizes ranging from 2 to 6. The researcher collecting the data is blinded to randomisation details (e.g., blocking). On intervention days, ice-lollies are offered to all eligible patients by the nursing staff in addition to standard of care refreshments at the same time point at which oral fluids are routinely offered, and always at nurse discretion. Patients must be sufficiently awake and able to safely hold and swallow oral intake. No formal recovery score threshold is applied. On control days there is standard of care without ice-lollies. Standard postoperative refreshments in our institution include water, coffee and biscuits. Nurses are notified of the randomisation result by personal communication and a large sign in the middle of the PACU. To ensure protocol adherence and prevent cross-contamination, the freezer is kept securely locked on control days when no ice-lollies are provided. Adherence to the intervention will be documented. On intervention days, it will be recorded whether an eligible patient was offered and consumed an ice lolly. Patients who decline the ice lolly despite being eligible will remain in the intention-to-treat analysis according to the randomized day. A per-protocol analysis will additionally be performed including only patients who received the allocated intervention as planned. Anonymised patient data is entered prospectively at the bedside by a dedicated study investigator directly into a password-protected electronic Case Report Form (eCRF) hosted on the secure intranet server. Access is restricted to the research team and all activities are logged. No direct personal identifiers (e.g., name, hospital number, case number) are recorded. K-anonymisation is ensured by generalization via binning (age, height, weight, procedure) in predefined ranges. Data completeness is monitored during entry with immediate correction of missing or implausible values. Data collection ends when the patient is discharged to the general ward without follow-up. Patients are not re-identifiable in the study database.

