#### Statistical analyses

After patient enrolment is finished, data will be analysed. There is no interim analysis planned due to the short study period. Patient characteristics and clinical data will be descriptively analysed as appropriate after visual normality check. The proportion of missing data is expected to be very low, as data are entered prospectively at the bedside by a dedicated study investigator. If missing data remain minimal, a complete-case analysis will be performed. If the proportion of missing data should exceed expectations, appropriate sensitivity analyses will be considered. The analysis will be conducted as Intention-to-Treat (ITT) in all randomized patients according to group assignment and Per-Protocol (PP) with all patients who received the assigned intervention as planned. All tests will be two-sided, with α = 0.05.

Baseline characteristics will be summarised descriptively by treatment group. Continuous variables will be reported as mean (standard deviation) or median (interquartile range), as appropriate. Categorical variables will be presented as counts and percentages. No formal statistical testing of baseline differences will be performed.

To account for the cluster-randomized design with randomization at the level of the day, all inferential analyses will be performed using mixed-effects regression models including a random intercept for cluster (day).

For the primary outcome (PACU length of stay), a linear mixed-effects model will be used. If substantial deviation from normality is observed, an appropriate generalized linear mixed-effects model (e.g., gamma distribution with log link) will be applied. Binary outcomes will be analysed using generalized linear mixed-effects models with logit link.

For medication dosage outcomes with a high proportion of zero values, a two-part modelling approach will be applied: first, a mixed-effects logistic regression model will analyse the probability of receiving any medication (yes/no); second, among patients receiving medication, dosage will be analysed using an appropriate mixed-effects model depending on distributional characteristics.

For the primary and secondary outcomes, age range, sex, ASA physical status, surgery type, and duration and type of anaesthesia will be included as covariates. For the secondary outcomes pain medication and nausea/vomiting, the duration of stay in the PACU is included as an additional covariate.

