One limitation of our study is the single-centre design. However, due to the cluster randomization, a high number of patients is expected to be enrolled in a short period of time. Furthermore, several patients who are offered ice-lollies will decline the intervention, which is the reason for the per-protocol analysis. Patients declining the intervention reflect real-world practice rather than protocol deviation. It is possible, that the number of patients actually accepting the intervention compared to the number of patients enrolled on control days will be considerably smaller, which could be another limitation. However, regarding the secondary outcomes, this trial includes 30 times more patients than the largest of the previous trials investigating the effects of this intervention; therefore, a conclusion based on sound data is expected. The strengths of our study are the blinding of the staff towards the primary outcome, the large number of patients and the pragmatic nature of the intervention. This protocol can serve as a template for a feasible study design in perioperative medicine.

In summary, we will perform a cluster randomized trial to test the hypothesis whether offering ice-lollies in the recovery area leads to a shorter length of stay in postoperative anaesthesia care.

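### The per-protocol set selects on receiving the lolly in one arm only, so its comparison carries selection bias of unknown direction and conflicts with the plan's own definition of the intervention

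*Protocol article*

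**What the plan says.** The section Protocol defines what is tested: "The intervention consists of offering ice lollies". The offer is made "at the same time point at which oral fluids are routinely offered, and always at nurse discretion". A condition is attached: "Patients must be sufficiently awake and able to safely hold and swallow oral intake". It has no objective cut-off: "No formal recovery score threshold is applied". Uptake is documented in one arm: "On intervention days, it will be recorded whether an eligible patient was offered and consumed an ice lolly". On control days the freezer is locked.

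Patients who decline stay in the intention-to-treat analysis. Then: "A per-protocol analysis will additionally be performed including only patients who received the allocated intervention as planned". The section Statistical analyses repeats the definition, listing after intention-to-treat a "Per-Protocol (PP) with all patients who received the assigned intervention as planned". It does not say in words which of the two is primary.

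The Discussion gives the expected number of decliners as the reason for the per-protocol analysis. Its next sentence reads: "Patients declining the intervention reflect real-world practice rather than protocol deviation". It then contrasts the number of patients accepting a lolly with the number enrolled on control days.

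**The concern.** A per-protocol set defined by receipt applies its filter in one arm only. On an intervention day a patient must be awake enough, be approached by a nurse and accept. On a control day the assigned care is the usual care, which practically everyone receives. Would-be decliners among controls cannot be identified, so they stay in.

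The filter is plausibly related to the outcome. The section Primary outcome bases discharge on, among other things, nausea and vomiting, the Glasgow Coma Scale, the Richmond Agitation-Sedation Scale and the delirium score. Alertness is a condition for receiving a lolly, and nausea may well reduce acceptance. Time is a second link: a patient judged ready before any offer was made cannot be a taker. Either link can produce a difference in stay between takers and all controls when the lolly does nothing.

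There is also a contradiction. If the intervention is the offer and declining is no deviation, a patient who was offered a lolly and declined was treated per protocol. Yet declining is the stated reason for the analysis that leaves such patients out.

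**Working it through.** **Step 1: the plan's target.** The section Sample size assumes a mean stay of 90 min and an SD of 40 min. A 5% reduction is 0.05 × 90 = 4.5 min, and 4.5 / 40 = 0.1125, which agrees with the stated 0.11. The bias is measured against 4.5 min.

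**Step 2: who is in each per-protocol group.**

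| | Intervention day | Control day |
|---|---|---|
| Assigned care | Offer of a lolly plus standard care | Standard care |
| Needed to count as received | Awake, approached by nurse, accepts | Nothing further |
| Offer and consumption recorded | Yes | No |
| Removed from the set | Decliners, patients not offered | Practically nobody |

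The control column is an inference from the sections Protocol and Statistical analyses and from the Discussion's comparison of acceptors with control-day patients. No single sentence states it.

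**Step 3: the bias under no effect.** Let u be the share of eligible patients who take the lolly, T the mean underlying stay of takers and N that of non-takers. Randomisation by day gives both arms the same mix in expectation:

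- mean of all controls = uT + (1 − u)N
- mean of the per-protocol intervention group = T
- difference = uT + (1 − u)N − T = (1 − u)(N − T) = (1 − u)D

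A positive value looks like a benefit of the lolly, a negative value like harm.

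**Step 4: numbers.** The article gives neither u nor D. Assumed: u from 60% to 80%, D from −15 to +15 min.

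| Uptake | D = −15 | D = −10 | D = 0 | D = +10 | D = +15 |
|---|---|---|---|---|---|
| 60% | −6.0 | −4.0 | 0 | +4.0 | +6.0 |
| 70% | −4.5 | −3.0 | 0 | +3.0 | +4.5 |
| 80% | −3.0 | −2.0 | 0 | +2.0 | +3.0 |

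The gap between non-takers and takers that equals the whole target is 4.5 / (1 − u): 11.25 min at 60%, 15 min at 70% and 22.5 min at 80%. On the SD of 40 min these are 0.28, 0.375 and 0.56 SD.

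**Step 5: does adjustment remove it?** The covariates for the primary outcome are age range, sex, ASA status, surgery type, and duration and type of anaesthesia. They may explain part of D. None measures alertness at the time of the offer, the nurse's decision or willingness to accept. After adjustment, D should be read as the remaining gap.

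**Step 6: which sign?** Drowsy or nauseated patients who never take a lolly make D positive. Patients judged ready before an offer make D negative. The article gives no figures to weigh these against each other.

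**The case against.** The tempting reading is that takers are the fitter patients, so the per-protocol analysis will flatter the lolly. The documents do not support that. Discharge itself requires acceptable neurological scores, and transfers to intermediate or intensive care are excluded, so most analysed patients become alert before the decision. The offer has no fixed early time, so drowsiness may delay it rather than prevent it, and a longer stay gives more opportunity to be offered a lolly. Swallowing difficulty is largely not a one-sided filter either, because the section Patients excludes it in both arms. All of this stands, and it is why D must be allowed to take either sign.

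A second defence is that the analysis is only additional. The hypothesis concerns offering, decliners are kept under intention-to-treat, and that analysis is listed first. This also stands. A reader might infer that the trial's main conclusion is at risk, but it is not. What remains is that the hierarchy is implied rather than stated.

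Third, detailed population definitions often sit in an analysis plan that is not shown. But the article itself defines the set by receipt, twice, and gives its reason. Reading receipt as having been offered a lolly would keep decliners in. The Discussion's reason for the analysis would then fail, and patients not offered one would still be dropped from one arm only.

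**Conclusion.** The point holds for the per-protocol analysis only. Selection after randomisation in one arm follows from the definition, while its direction and size are not established. Under assumed uptake of 60% to 80% and an underlying gap of −15 to +15 min, a lolly with no effect would show a difference of about −6 to +6 min, a range that includes zero and extends beyond the 4.5 min target on both sides. A per-protocol result in either direction could therefore not be read as the effect of eating the lolly. The calculation rests on essentially all control-day patients being in the comparison, which is inferred, and on the assumed uptake and gap. The contradiction with the definition of the intervention and with the statement on decliners rests on no assumption. Intention-to-treat is sound.

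**What to change.** 1. State that intention-to-treat by randomised day is the primary analysis.
2. Define the per-protocol set by day: exclude only days on which the allocation was not carried out, and keep decliners and patients not offered a lolly. This removes the patient-level selection and agrees with the Discussion's view of decliners. If every day ran as allocated, the set equals the intention-to-treat set.
3. If an effect of eating the lolly is wanted, report as a secondary analysis a complier-average effect: the intention-to-treat difference divided by documented uptake, with the randomised day as instrument and day-clustered standard errors. The locked freezer makes uptake on control days zero by design. For example, 2.7 min at 60% uptake gives 2.7 / 0.6 = 4.5 min.

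The cost is wording, since uptake is already recorded. The complier-average interval is wider: with uptake treated as known, by 1 / 0.6 = 1.67 at 60% and 1 / 0.8 = 1.25 at 80%. It adds essentially no independent test beyond intention-to-treat. It also assumes that the allocated day affects stay only through eating the lolly. That is questionable here, because nursing staff are unblinded, a large sign shows the allocation, and a declined offer may itself have an effect. The report should say so. Recruitment was expected to end in February 2026, so the change should be dated and made before outcomes are compared by arm.

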### Safety considerations

Patients with diabetes or impaired glucose tolerance are not excluded from participation. Blood glucose monitoring and management are part of routine postoperative care in the PACU, and clinically relevant deviations are treated according to institutional protocols. The carbohydrate content of the intervention is comparable to standard postoperative oral intake and does not introduce additional risk beyond usual care.

### Outcomes

#### Primary outcome

The primary outcome is the time spent in the PACU from admission after surgery to the decision to discharge by the attending nurses and physicians. Time of decision to discharge instead of time of discharge was chosen to avoid procedural delays of patient transfer to the general ward due to staff shortage. PACU discharge is based on a standardized and routinely documented clinical assessment. This includes evaluation of respiratory and circulatory stability, temperature, urine output, bleeding, nausea/vomiting, sensibility and motor function, as well as neurological status assessed using the Glasgow Coma Scale, the Richmond Agitation-Sedation Scale, and the NUDESC score. Patients are discharged to the ward once all parameters are within acceptable clinical limits according to institutional practice.

#### Secondary outcome

Three secondary outcomes have three main components: pain, nausea and vomiting, and delirium. Pain includes the visual analogue scale at admission and discharge, and consumption of pain medication such as opioids, NSAID, metamizole and paracetamol. Nausea and vomiting is documented as separate outcomes, in addition the administration of any antiemetic medication intra- or postoperatively is recorded. Delirium is defined as a Nursing Delirium Screening Scale (NUDESC) at discharge ≥ 2. The NUDESC is also the communicated primary outcome to the staff and study team involved in data collection.

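### VAS pain at PACU admission is a pre-intervention value, but it is listed within the pain outcome and left out of the stated covariates, so precision is given away

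*Protocol article*

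**What the plan says.** The Secondary outcome section of the protocol article defines the pain component as follows: "Pain includes the visual analogue scale at admission and discharge", together with the use of analgesics. The admission and discharge scores stand side by side, with no difference in role.

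The Protocol section places the intervention in the PACU, "at the same time point at which oral fluids are routinely offered, and always at nurse discretion". It also requires that the patient be awake enough to hold and swallow safely.

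The Statistical analyses section gives one covariate list for the primary and secondary outcomes: "age range, sex, ASA physical status, surgery type, and duration and type of anaesthesia will be included as covariates". It then makes one outcome-specific addition: "For the secondary outcomes pain medication and nausea/vomiting, the duration of stay in the PACU is included as an additional covariate". Admission VAS appears in neither place. All inferential analyses are mixed-effects models with a random intercept for day, and for dosage outcomes with many zeros the plan is specific: "For medication dosage outcomes with a high proportion of zero values, a two-part modelling approach will be applied".

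**The concern.** A score taken on arrival in the PACU cannot respond to something offered later in the stay. Comparing it between arms says nothing about the intervention, so it does not belong among the outcomes. Its natural use is as a baseline measurement of the same quantity that is compared at discharge, and the plan does not use it that way.

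The plan does make an outcome-specific choice of covariate. It picks duration of PACU stay, which is observed after the intervention and is itself the primary outcome, and leaves out a pre-intervention pain score that is already in the case report form.

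At stake is the width of the confidence intervals for the pain comparisons. This matters most in the surgical subgroups, which the Discussion wants to use to separate a local cold effect in ENT patients from a more general effect on pain. Those groups are smaller than the whole trial.

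**Working it through.** **Order of events.** The day is randomised in the morning, the patient arrives in the PACU (admission VAS), fluids and possibly a lolly are offered, and discharge is decided (discharge VAS). The admission score therefore comes before exposure for every patient.

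**The plan's own sample size.** The plan states no figure for the pain outcomes. Its only calculation is for length of stay, and it is used here just to obtain an effective sample size.
- Inputs (Sample size section): difference 4.5 min, SD 40 min, two-sided α 0.05, power 80%, 30 patients per day, ICC 0.01.
- Per arm: 2 × (1.960 + 0.842)² × (40/4.5)² gives 1,241, so 2,482 in total. With d rounded to 0.11 the total is 2,596, which matches the stated figure of about 2,600.
- Design effect: 1 + (30 − 1) × 0.01 = 1.29.
- 2,482 × 1.29 = 3,202, which is 2.0% above the stated 3,140 and close enough for this purpose.
- Effective total at 3,140: 3,140 / 1.29 = 2,434.

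**Discharge VAS without admission VAS.** In SD units the standard error of the difference is 2/√2,434 = 0.0405. The difference detectable with 80% power is 2.8016 × 0.0405 = 0.114 SD.

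**Discharge VAS with admission VAS as a covariate.** If r is the correlation between the two scores given the covariates already listed, the variance is multiplied by 1 − r² and the detectable difference by √(1 − r²). The documents give no value of r, so a range is assumed.

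| Assumed partial r | Variance factor 1 − r² | Detectable difference (SD) | Equivalent sample-size ratio 1/(1 − r²) |
|---|---|---|---|
| not adjusted | 1.00 | 0.114 | 1.00 |
| 0.3 | 0.91 | 0.108 | 1.10 |
| 0.5 | 0.75 | 0.098 | 1.33 |
| 0.7 | 0.51 | 0.081 | 1.96 |

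**Limits of the calculation.** It carries the ICC for length of stay over to VAS and assumes that adjustment shrinks the within-day and between-day variance in the same proportion. It applies to a linear model for discharge VAS. The logistic part of the medication analysis does not follow the same formula, so a gain there is probable but not quantified.

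**The case against.** **Omission does no harm under randomisation.** This stands. Leaving out a baseline value does not bias a randomised comparison, and a chance imbalance in admission pain is ordinary sampling error that the confidence interval already covers. The point is about precision only.

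**The gain may be small.** This stands in part. Age, sex, ASA status, surgery type, and duration and type of anaesthesia are already adjusted for, so only the partial correlation counts. At 0.3 the detectable difference moves merely from 0.114 to 0.108 SD. The outcome is secondary, in a study that the protocol calls exploratory.

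**The admission score may be meant as a reference for discharge, with details left to the statistical analysis plan.** The wording allows the first, and a separate plan is said to exist. But the article does not leave the covariates open. It gives an explicit list with an outcome-specific addition, and admission pain is in neither. That is a choice made in this document, and it can be commented on.

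**A stronger reading that the text does not support.** A reader might infer from "in addition the administration of any antiemetic medication intra- or postoperatively is recorded" that prophylaxis given in the operating room is pooled with PACU treatment into one endpoint, so that a real effect on postoperative use would be diluted. The article says only that administration is recorded. It defines no combined endpoint. Antiemetic use is not among the secondary outcomes named in the Abstract and Background, nor among the outcomes named in the Statistical analyses section. Recording the two periods apart fits the sentence equally well. A power loss could be computed only from invented antiemetic rates for an analysis the plan does not describe, so none is given.

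**Conclusion.** The point holds as a loss of precision on secondary pain outcomes. Admission VAS is collected before the intervention, is presented as part of the outcome, and is missing from a stated covariate list. No bias follows, and the primary analysis and the 3,140 patients are unaffected.

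The size is unknown because the documents give no correlation. Over assumed partial correlations of 0.3 to 0.7, between 9% and 49% of the residual variance of discharge VAS could be removed. For analgesic use the direction is likely the same, but no figure can be given. That pooled antiemetics dilute a comparison is not established.

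**What to change.** In the Secondary outcome section, name discharge VAS and pain-medication consumption as the pain outcomes, and describe admission VAS as a baseline measurement. In the Statistical analyses section, add admission VAS as a covariate in the mixed models for discharge VAS and for pain-medication use (both parts of the two-part model), and report it by arm in the baseline table.

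Two details should be settled at the same time:
- State how a missing admission score is handled, so that adding the covariate does not remove patients from a complete-case analysis.
- Note that the score is taken after the day's allocation is known in the PACU. The baseline table should therefore show whether it looks alike in both arms.

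If antiemetic use is to be analysed at all, one sentence is enough: only administration after PACU admission counts as the outcome, and intraoperative antiemetics enter as a covariate. This requires that the case report form keeps the two periods apart.

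For the pain outcomes the cost is wording only. The data are already being collected, and no patients or procedures are added. The change should be dated and made before the data are analysed by arm.
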